### Study Interventions

#### Study App

The study app was developed by Dublin City University (AthenaCX, DCU). It allows researchers to rapidly design and deploy mobile experience sampling apps (iOS and Android), including integrated consenting and wearable data collection devices. This will provide the participants with a study overview in the form of plain language statements and privacy statements and facilitate the participants e-consent into the study. The app was designed to ensure that subjects have read the study details and consented to the study before completing the study assessments (Multimedia Appendix 1 includes a text sample from the plain language statement and informed consent in the mobile app). The participants have the right to withdraw from the study at any time. The app will be used to deliver the assessments and provide a link to the decision-making game. Push notifications will be sent to the participants during the study, requesting them to complete the assessments at the required time intervals, as detailed below.

#### Fitbit

The use of fitness trackers in this study will facilitate the objective assessment of the participants’ activity patterns and behavioral changes in exercise. It will also enable the identification of individuals who already have a well-established exercise regime. A BYOD approach will be used, and data from each participant’s Fitbit will be captured. Fitbit devices are a range of physical activity trackers and smartwatches that combine integrated accelerometers and photoplethysmograph sensors to measure motion and heart rate. Proprietary algorithms convert the accelerometer data into sleep and activity patterns. Fitbit devices use Bluetooth low energy technology to synchronize with the individual’s mobile device and produce various metrics, including step count, floors climbed, distance covered, calories burned, active minutes, sleep time and stages, and heart rate. In this study, a high-frequency intraday data will be collected using a web-based application programming interface. These data are highly granular and include 1 minute and 15 minutes for activity and 1 second and 1 minute for heart rate.

### Assessments

#### Demographic Information

Participants will be requested to provide details of their age and sex. The following classifiers will be used: male, female, self-defined, and prefer not to say.

#### Self-efficacy Questionnaire

The self-efficacy questionnaire for exercise was based on the Bandura Exercise Self-Efficacy scale initially developed in 2006 [26], and the original 0 to 100 numerical rating scale was used (Multimedia Appendix 1). Participants were asked to rate their degree of confidence by moving a widget across a scale on the app. A rating of 0 equates to *cannot do at all* and a rating of 100 reflects complete confidence and participants are *highly certain* they can engage in physical activity. Participants will be requested to complete the self-efficacy questionnaire at the start of the study and 6 months after the study commencement (Multimedia Appendix 2 includes the self-efficacy questionnaire and screenshots of the app).

#### Status of Change

To ensure that all participants were able to assess their current activity levels against the same criteria, the WHO physical activity guidance [27] was included in the instructions for the *stages of change* questionnaire. Participants were asked to consider only planned physical activities aimed at improving or maintaining physical fitness and health. Active periods should consist of 150 minutes of moderate-intensity physical activity (such as a brisk walk) in a week or 75 minutes of vigorous-intensity physical activity (such as a jog or run) over the course of a week. Participants will be asked to complete the status of changes questionnaire at the start of the study and 6 months after study commencement (Multimedia Appendix 3 includes details of the stages of change questionnaire and screenshots of the app).

#### Type D Personality Questionnaire

The 14-question Type D personality questionnaire developed by Denollet [16] will be used in this study. A total of 7 questions pertain to the negative affectivity domain and 7 to the social inhibition domain. Each question will be scored on a scale of 0 to 4. The questionnaire will be scored as individual negative affectivity and social inhibition domains and a composite Type D personality score. Participants will be asked to complete the Type D personality questionnaire at the start of the study and 6 months after the study commencement (Multimedia Appendix 4 includes details of the Type D personality questionnaire and screenshots of the app).

#### Decision-making Tasks

These tasks will be performed twice during the study. The IGT will be deployed within the first 3 months and at 6 months. Participants in the IGT will be given €2000 (US $2314) virtual money and presented with 4 decks of cards labeled A, B, C, and D. Each card in these decks can generate wins and can sometimes cause losses. Participants must choose 1 card from these 4 decks consecutively until the task shuts off automatically after 100 trials. In each trial, feedback on rewards and losses of their choice and the running tally over all trials so far are given to the participants, but no information is given regarding how many trials they will play and how many trials they have completed during the task. Participants will be instructed to choose cards from any deck and switch decks at any time. They will also be told to make as much money as possible, minimizing losses.

Table 1 presents the payoff for the 4 decks. As seen in the table, decks A and B are 2 “bad decks” that generate high immediate, constant rewards but even higher unpredictable, occasional losses. Thus, the long-term net outcome associated with decks A and B is negative. In contrast, decks C and D are 2 “good decks” that generate low immediate, constant rewards but even lower unpredictable, occasional losses. Thus, the long-term net outcome associated with decks C and D is positive. In addition to the payoff magnitudes, the 4 decks also differ in the frequency of losses, that is, decks A and C are associated with a higher frequency of losses, whereas decks B and D are associated with a lower frequency of losses. The key to obtaining a higher long-term net outcome in this task is to explore all the decks in the initial stage and then exploit the 2 good decks (Figure 1 shows a screenshot of the web-based IGT implemented).

**Table 1 table1:** Summary of the payoff of the Iowa Gambling Task.

Characteristics	Deck A (bad deck with frequent losses)	Deck B (bad deck with infrequent losses)	Deck C (good deck with frequent losses)	Deck D (good deck with infrequent losses)
Reward/trial	100	100	50	50
Number of losses/10 cards	5	1	5	1
Loss/10 cards	−1250	−1250	−250	−250
Net outcome/10 cards	−250	−250	250	250

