**Objective:**

The aim of this study is to determine whether it is possible to use decision-making tasks such as the Iowa Gambling Task to help determine those most likely to abandon their fitness goals. Predictive models built using methods from computational models of decision-making, combining objective data from a fitness tracker with personality traits and modeling from decision-making games delivered via a mobile app, will be used to ascertain whether a predictive algorithm can identify digital personae most likely to be nonadherent to self-determined exercise goals. If it is possible to phenotype these individuals, it may be possible to tailor initiatives to support these individuals to continue exercising.

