## Introduction

### Background

As a society, we are becoming more sedentary. In some countries, inactivity levels can be as high as 70%, with 1 in 4 adults and 3 in 4 adolescents not achieving the recommended World Health Organization (WHO) activity levels [1]. Recommendations for adults are as follows: “at least 150 minutes of moderate-intensity aerobic physical activity throughout the week or do at least 75 minutes of vigorous-intensity aerobic physical activity throughout the week or an equivalent combination of moderate- and vigorous-intensity activity” [2]. In a press release issued to celebrate world health data on April 7, 2020, the WHO stated that approximately 2 million deaths per year are due to low physical activity. From a global perspective, sedentary behavior is one of the 10 leading causes of mortality and morbidity [1]. Physical inactivity can significantly affect an individual’s health and quality of life and increase the probability of developing several chronic diseases such as heart disease, obesity, high blood cholesterol, and type 2 diabetes.

Every year, a large section of the global population makes resolutions that are focused on improved fitness. Unfortunately, these resolutions are not sustained, with both popular media and peer-reviewed journals reporting on the low number that maintain behavioral changes. Popular media report dramatic figures, including an analysis by Strava of their global membership data, revealing that January 17, 2020, was *quitters day*, the day individuals are most likely to give up their New Year’s resolutions [3]. Similar statistics have been reported for gym membership and use. A review by Sperandei et al [4] of over 5240 gym members revealed a dropout rate of 47% by the second month, 86% by the sixth month, and 96% by the 12th month. These figures were reinforced by a Spanish study of 14,522 gym members, which revealed that between 47.3% and 56% dropped out over the course of a year [5].

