In a study by Bechara, a discernible difference in deck selection was identified when performance of healthy participants was compared with that of a clinical population. Although initially, the IGT was used in subjects with damage to the ventromedial prefrontal cortex, it has been used in a broader range of clinical patients and healthy populations to detect risky decision-making. Within the clinical context, the IGT has been used in several populations where decision-making is impaired, such as gambling, substance abuse, and several neurological conditions such as schizophrenia and psychopathy [30] and eating disorders [31]. Regarding healthy populations, some work has been done to show a differential response depending on whether individuals self-select as either an intuitive (affective) decision-making style or deliberate (planned) decision-making style, potentially those with a more intuitive decision-making style having greater success on the IGT [32]. Research in the '80s and '90s suggested a possible link between negative mood and decision-making behavior [33,34]. Suhr et al [35] built on these findings and investigated the impact personality traits have on the IGT’s performance. In 2007, they published the research results on 87 nonclinical participants, which showed that higher negative mood correlated with risky performance on the IGT. In 2013, the team identified a correlation among mood, personality variables, and deck selection. Although this study did not identify a link between positivity and a specific deck selection, less advantageous decks were selected by individuals in a more negative mood [36]. Although not without distractors, these findings were supported by the Somatic Marker Hypothesis, which postulates that emotional defects significantly impact what is understood as the normal decision-making process [37]. The hypothesis also specifies the number of structures and operations required for the normal decision-making operations.

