### Recruitment

The study will be advertised on social media, commencing in 2021. This is an entirely virtual, BYOD study design, and interested individuals without any underlying health issues and over the age of 18 years will be invited to download the study app from the Google Play store (Alphabet Inc) and Apple App Store (Apple Inc). Those who are willing to consent to the study and own a Fitbit (Fitbit Inc) will be requested to participate in the study. Once consent is given to participate in the study, participants will be asked to share their Fitbit data. Physical activity, sleep, and heart rate data will be shared using an anonymized token system to ensure that only pseudonymized data are included in the study. Once the individuals provide consent to participate in the study and share their Fitbit data, they will be asked to complete the following assessments: demographics, Type D personality, goal-setting, and self-efficacy questionnaire. They will also be asked to perform decision-making games based on the IGT.

Metrics concerning compliance with each assessment will be quantified. Data will be captured over 12 months. At the end of the study period, participants will be sent a notification to thank them for their participation and a link to where the study results will be shared once available.

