### Data Analysis and Computational Modeling

This study aims to investigate whether we can predict adherence to self-made fitness goals and identify potential behavioral phenotypes based on the changes in the participants’ responses to a series of validated instruments, including self-efficiency, status of change, and Type D personality, and their behavioral performance on the IGT over 6 months. A range of data analysis techniques will be applied to the collected data to achieve this goal.

We term the results obtained from questionnaires and decision-making tasks as predictor variables, whereas the adherence levels of the participants to fitness goals as target variables for convenience of description. The first problem that must be addressed before predicting and clustering is to quantify both the predictor variables and target variables.

Self-efficiency was measured by an instrument including 18 items using the original 0 to 100 numerical rating scale, where 0 represents *cannot do at all* and 100 represents *high certainty to do.* The Type D personality questionnaire also uses numerical rating scales, although with different ranges from 0 representing *false* to 4 representing *true*. However, for the Status of Change questionnaire, the answers were categorical scales of *yes* or *no*. Thus, the one-hot encoding technique, one of the most common encoding methods in machine learning, will convert the categorical answers to numerical formats.

To evaluate participants’ performance on the IGT, both superficial behavioral variables and underlying cognitive parameters will be summarized and estimated from the behavioral data set. Specifically, 2 parameters will be measured in the behavioral summary analysis. The first parameter will be the total amount of gain by the end of the task, and this parameter will be used to measure the overall performance of the IGT. The second parameter will be the IGT learning scores across the task, that is, the difference between the number of good deck selections and that of bad deck selections across the task, used to reflect the learning process in the task. The 100 trial choices will first be divided into five blocks of 20 trials, each without overlap, and the learning score will be calculated for each block. As a result, 5 variables (learning scores) will be created for this measure.

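### The first Iowa Gambling Task has a 3-month window while adherence is summed from the first week, so up to a quarter of the outcome can precede its headline predictor

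*Protocol article*

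**What the plan says.** The Objective gives the IGT the leading role. The aim is to "use decision-making tasks such as the Iowa Gambling Task to help determine those most likely to abandon their fitness goals". Data Analysis and Computational Modeling confirms that role: "We term the results obtained from questionnaires and decision-making tasks as predictor variables".

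Timing differs between the predictors:

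- **IGT** (Decision-making Tasks): "The IGT will be deployed within the first 3 months and at 6 months".
- **Self-efficacy** (Self-efficacy Questionnaire): "Participants will be requested to complete the self-efficacy questionnaire at the start of the study and 6 months after the study commencement".
- **Type D personality** (Type D Personality Questionnaire): "Participants will be asked to complete the Type D personality questionnaire at the start of the study and 6 months after the study commencement".
- **Status of change**: the same two time points as the other questionnaires.

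Recruitment lists the assessments requested after consent and adds, "They will also be asked to perform decision-making games based on the IGT". It names no day.

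The target is defined in Data Analysis and Computational Modeling. Each week scores 1 if the WHO activity minimum is met and 0 otherwise, and all weeks are summed. Recruitment sets data capture at 12 months. Nothing in the article starts the count after the IGT or brings the IGT date into the model.

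**The concern.** A predictor should be measured before the outcome it predicts. Here the questionnaires meet that condition at their first administration, and the IGT need not. The outcome starts to accrue in week 1, while the first IGT may come as late as the end of month 3.

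Two distortions could follow:

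- **Direction.** Someone who has already lapsed may play differently because of it. The Introduction reports from earlier work that "less advantageous decks were selected by individuals in a more negative mood". If lapse goes with lower mood, an IGT played afterwards could appear to foretell a lapse that came first.
- **Selection.** The IGT is reached through a separate web link, and participants receive no incentive. People who quit early are plausibly the least likely to complete a task sent weeks later, yet they are the people the model is meant to find.

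The claim at stake is the study's central one, that the IGT helps to identify in advance who will give up.

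**Working it through.** The article gives no figure of its own for this point, so there is none to reproduce. The check has four steps.

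**1. Target weeks that can precede the first IGT.** Three months is about 13 weeks and follow-up is about 52 weeks. 13/52 = 25% at most. With the IGT at the start the share is 0. For the month-6 sitting it is 26/52 = 50%.

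**2. Inputs for an illustration.** From Background, the first gym study reports "a dropout rate of 47% by the second month, 86% by the sixth month, and 96% by the 12th month", and the second reports 47.3% to 56% over a year. My assumptions are: IGT dates uniform over months 0–3; every participant has a date, independent of stopping; stopping is permanent; linear interpolation for the first study and a constant hazard for the second. S(t) is the proportion still active at month t.

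**3. Share stopped by their own IGT date** = 1 − (1/3)∫₀³ S(t) dt.

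- First study: S(0) = 1, S(2) = 0.53, S(6) = 0.14, S(12) = 0.04. By interpolation S(3) = 0.53 − (0.39/4) = 0.4325.
  - Area for months 0–2 = 2 × (1 + 0.53)/2 = 1.53. Area for months 2–3 = (0.53 + 0.4325)/2 = 0.48. Sum = 2.01.
  - Share stopped = 1 − 2.01/3 = 0.33, or about 66 of 200. A piecewise-constant hazard gives 0.36, or about 71 of 200.
- Second study: hazard λ = −ln(1 − q)/12.
  - q = 0.473: λ = 0.0534, area over 3 months = 2.77, share = 1 − 2.77/3 = 0.076.
  - q = 0.56: λ = 0.0684, area = 2.71, share = 1 − 2.71/3 = 0.096.

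**4. Share of adherent time before the person's own IGT** = ∫₀³ S(t)(1 − t/3) dt ÷ ∫₀¹² S(t) dt. The factor 1 − t/3 is the probability that the IGT has not yet been taken at time t.

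- First study: numerator = 1.072 (months 0–2) + 0.083 (months 2–3) = 1.155. Denominator = 1.53 + 1.34 + 0.54 = 3.41. Ratio = 0.34.
- Second study, q = 0.473: 1.423/8.861 = 0.16.
- Second study, q = 0.56: 1.402/8.185 = 0.17.

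For reference, with no dropout at all the same uniform dates give 1.5/12 = 12.5%.

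**The case against.** Several stronger readings are tempting, and the article does not support them.

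- **That two sections contradict each other.** Recruitment mentions the IGT alongside the enrolment requests but gives no day, and Decision-making Tasks supplies the timing. The two are compatible.
- **That each participant plays at a different time.** The window permits this but does not state it. Assessments are pushed by the study, and one common push day may be set in a fuller document. A common day late in the window would still have the problem, though: 47% had dropped out by month 2 in the first cited study.
- **That many will have given up before they play.** This depends on the source: about 33% in one study and 8–10% in the other. Both are gym-member cohorts. The target here is a weekly score that people can miss and then meet again, so the plan has no stopping event. The 33% also assumes that everyone plays. If early quitters skip the task, fewer actual sittings follow a lapse, and the problem becomes selective missingness.
- **That 59% of adherent time is lost to the window.** 2.01/3.41 = 59% is all adherent time in months 0–3. It would precede the IGT only if everyone played at the end of month 3.
- **That low mood causes poor play after a lapse.** The article reports an association between mood and deck choice, and nothing on lapse lowering mood. Reverse direction is a hypothesis.

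Two further objections stand and affect the remedy. Adding a 100-trial task at onboarding is a burden on unpaid participants, and the article already expects some incomplete IGTs. Moving the first sitting also does not help the month-6 predictors, which follow about half the target weeks in any case.

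**Conclusion.** The concern holds in a limited form. The 3-month window and a target that counts every week do not fit together, because up to about 13 of 52 target weeks (25%) can come before the headline predictor is measured. That bound needs no assumption about dropout. The illustrative figures of 33% or 8–10% stopped by the IGT date, and 34% or 16–17% of adherent time before it, rest on uniform dates, full IGT completion and gym-member dropout. They show a range and do not forecast this cohort.

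An analysis plan that is not shown could restrict the target weeks. It could not recover a pre-lapse IGT that was never taken. The point should be settled before the first push notifications go out. The article describes recruitment as pending at submission.

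**What to change.** 1. Prompt the first IGT at enrolment with the questionnaires, set a short completion limit (14 days, for example), and record the completion date.
2. Define the target for every participant from one common landmark after the first IGT, or as the proportion of observed weeks after it in which the activity minimum was met. Do not drop early weeks from a raw sum for late players only. Someone who plays at week 13 could then score at most 39 against 52 for others, which creates a new artefact.
3. Use month-6 IGT results, month-6 questionnaires and all change scores only to predict adherence after month 6.
4. Report how many participants never complete the first IGT, and compare their adherence with that of completers.

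The cost is a change to notification timing, a few sentences of analysis text, somewhat more burden at onboarding, and fewer target weeks: those before the landmark for the main model, and about 26 of 52 for any model that uses month-6 predictors.

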**Figure 1 figure1:**
[figure not shown]
Screenshot of the web-based Iowa Gambling Task.

### Data Analysis and Computational Modeling

This study aims to investigate whether we can predict adherence to self-made fitness goals and identify potential behavioral phenotypes based on the changes in the participants’ responses to a series of validated instruments, including self-efficiency, status of change, and Type D personality, and their behavioral performance on the IGT over 6 months. A range of data analysis techniques will be applied to the collected data to achieve this goal.

We term the results obtained from questionnaires and decision-making tasks as predictor variables, whereas the adherence levels of the participants to fitness goals as target variables for convenience of description. The first problem that must be addressed before predicting and clustering is to quantify both the predictor variables and target variables.

Self-efficiency was measured by an instrument including 18 items using the original 0 to 100 numerical rating scale, where 0 represents *cannot do at all* and 100 represents *high certainty to do.* The Type D personality questionnaire also uses numerical rating scales, although with different ranges from 0 representing *false* to 4 representing *true*. However, for the Status of Change questionnaire, the answers were categorical scales of *yes* or *no*. Thus, the one-hot encoding technique, one of the most common encoding methods in machine learning, will convert the categorical answers to numerical formats.

To evaluate participants’ performance on the IGT, both superficial behavioral variables and underlying cognitive parameters will be summarized and estimated from the behavioral data set. Specifically, 2 parameters will be measured in the behavioral summary analysis. The first parameter will be the total amount of gain by the end of the task, and this parameter will be used to measure the overall performance of the IGT. The second parameter will be the IGT learning scores across the task, that is, the difference between the number of good deck selections and that of bad deck selections across the task, used to reflect the learning process in the task. The 100 trial choices will first be divided into five blocks of 20 trials, each without overlap, and the learning score will be calculated for each block. As a result, 5 variables (learning scores) will be created for this measure.

Cognitive parameters that drive the behavioral performance will be extracted from the cognitive models designed for the IGT. As mentioned earlier, multiple models have been proposed for the IGT, including the Expectancy-Valence Learning model, the PVL-Delta model, the PVL-Decay model, the Value-Plus-Perseverance model, and the latest proposed Outcome-Representation Learning model (Table 2 presents the parameter specifications of the 4 IGT models). The hierarchical Bayesian modeling method, where both individual and group parameters (ie, posterior distributions) are estimated simultaneously in a mutually constraining fashion, will be used to estimate the cognitive parameters for each model. The models will be implemented in a newly developed probabilistic programing language STAN, which uses a specific Markov Chain Monte Carlo sampler called Hamiltonian Monte Carlo, to efficiently perform sampling from high dimensional posterior distributions as specified by the user. After obtaining the fitting results, model validation will be executed to determine the winning model, including a one-step-ahead leave-one-out information criterion and a posterior predictive check. The parameters of the winning model will then be used as predictor variables to predict adherence behavior. Thus, the number of variables obtained here for predicting adherence depends on which model best fits the data set.

**Table 2 table2:** Parameter specifications of the 4 Iowa Gambling Task models.

Model	NP^a^	Parameters							
PVL^b^_delta	4	Outcome sensitivity (α)	Loss aversion (λ)	Learning rate (*A*)	Response consistency (c)	N/A^c^	N/A	N/A	N/A
PVL_decay	4	Outcome sensitivity (α)	Loss aversion (λ)	Decay parameter (*A*)	Response consistency (c)	N/A	N/A	N/A	N/A
VPP^d^	8	Outcome sensitivity (α)	Loss aversion (λ)	Learning rate (*A*)	Decay parameter (*K*)	Gain impact parameter (*EP*_P_)	Loss impact parameter (*EP*_N_)	Weight parameter (*w*)	Response consistency (c)
ORL^e^	5	Reward learning rate (A_+_)	Punishment learning rate (A_–_)	Decay parameter (*K*)	Outcome frequency weight (*ß*_F_)	Perseverance weight (*ß*_p_)	N/A	N/A	N/A

^a^NP: number of parameters.

^b^PVL: Prospect Valence Learning.

^c^N/A: not applicable.

^d^VPP: Value-Plus-Perseverance.

^e^ORL: Outcome-Representation Learning.

Finally, the question arises of how to quantify the target variable, that is, the adherence behavior, given that various types of objective fitness data will be collected. We will mainly rely on the data set of activity patterns and the step counts. According to the WHO physical activity guidelines, to improve or maintain physical fitness and health, active periods should consist of 150 minutes of moderate-intensity brisk walking or 75 minutes of vigorous-intensity jogging or running over the course of a week. If the participant completes this minimum exercise in a particular week, their adherence score for this week will be 1; otherwise, the score is 0. The scores for all weeks will be summed to obtain a total score to represent the overall adherence level of this participant.

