### Type D Personality

A Type D personality is a term used to describe a personality type that tends to have negative affectivity and social inhibition [16]. Denollet [17] developed the DS14, a validated psychometric measure for assessing negative affectivity, social inhibition, and Type D personality types, and as early as 1998, it showed a demonstrable link between Type D personality and coronary heart disease. According to a 2005 study of over 3800 subjects, this 14-item questionnaire was observed to be stable over 3 months and not dependent on mood and health status [16]. Type D personality has been associated with medication nonadherence and heart failure [18], coronary heart disease [19], and type 2 diabetes [20,21]. Several studies have linked Type D personalities with sedentary lifestyles, including a 2009 study of 564 healthy men that showed that Type D personality was more common in men with a sedentary lifestyle (45%) than men who exercised regularly (14%) [20]. Compared with non-Type D personality types, Type D personality types have been associated with decreased walking and total exercise [22]. This study of 189 healthy volunteers looked at the relationship between Type D personality, physical activity, and self-efficacy and determined that Type D personalities had lower levels of self-efficacy and engaged in significantly less walking and total exercise compared with non-Type D personalities [22].

Low self-efficacy has been associated with Type D personalities in populations with chronic diseases such as type 2 diabetes [23] and acute coronary syndrome [19].

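### Adherence is to be predicted from 6-month changes, but the target counts all weeks of the 12 months, so about half of it precedes those predictors

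*Protocol article*

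**What the plan says.** **Predictors.** The Data Analysis and Computational Modeling section gives one aim with two parts: to predict adherence and to "identify potential behavioral phenotypes based on the changes in the" participants' answers on self-efficacy, status of change and Type D, together with "their behavioral performance on the IGT over 6 months". It continues: "We term the results obtained from questionnaires and decision-making tasks as predictor variables". It does not restrict these to a time point.

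**Timing.** Participants "complete the self-efficacy questionnaire at the start of the study and 6 months after the study commencement". The Status of Change and Type D sections give the same two time points. For the IGT, the Decision-making Tasks section says: "The IGT will be deployed within the first 3 months and at 6 months". The Recruitment section lists the IGT with the assessments requested after consent, and sets data capture at 12 months.

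**Target.** Each week scores 1 if the WHO minimum (150 minutes moderate or 75 minutes vigorous activity) is met, and 0 otherwise. Then: "The scores for all weeks will be summed to obtain a total score to represent the overall adherence level of this participant". No weeks are excluded and no landmark is set.

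**Purpose.** The Objective, Study Hypothesis and Discussion all present the model as a way to find likely quitters so that support can be directed to them.

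**The concern.** A prediction model is useful here only if its inputs exist before the behaviour it predicts. A 6-month change does not exist until month 6, yet the target already contains every week up to then. Take a participant who meets the criterion through week 6 and then stops for good. The whole score of 6 is settled 20 weeks before the change is measured.

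The protocol itself supplies a route by which lapsing could move the predictors. Its Status of Change section says that people can regress to previous stages and that self-efficacy is thought to shift as they move between stages. The status of change questionnaire also carries the WHO 150/75-minute guidance in its instructions, and the target is scored on that same threshold. The month-6 answer is thus close to a self-report of part of the outcome.

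At stake is the headline claim. A well-fitting model could be describing who has already lapsed, and it would offer nothing for someone who stopped before month 6.

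**Working it through.** The article gives no figure for this point, so there is nothing to reproduce. The check concerns timing, followed by what can be said about size.

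**1. Overlap of the windows** (12 months taken as 52 weeks)
- Weeks before the month-6 measurements: 52 × 6/12 = 26, or 50% of the target.
- Weeks before the first IGT, if taken at the 3-month limit: 52 × 3/12 = 13, or 25%. This is a maximum.

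**2. How many might have stopped by then**

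The article states no rate for this study. The Background section cites two gym-membership sources: "a dropout rate of 47% by the second month, 86% by the sixth month, and 96% by the 12th month", and 47.3% to 56% over a year. Let S(t) be the proportion not yet stopped at month t. I assume a constant hazard between quoted points.

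- First source: S(2) = 0.53 and S(6) = 0.14. Monthly hazard = ln(0.53/0.14)/4 = 0.333. S(3) = 0.53 × exp(−0.333) = 0.38, so 62% stopped by month 3. The 86% by month 6 is quoted directly.
- Second source, with annual dropout d: proportion stopped by month m = 1 − (1 − d)^(m/12).

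| Source | By month 3 | By month 6 |
|---|---|---|
| 47%/86%/96% curve | 62% | 86% |
| d = 0.473 | 14.8% | 27.4% |
| d = 0.56 | 18.6% | 33.7% |

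The ranges are about 15% to 62% by month 3 and 27% to 86% by month 6. Linear interpolation gives 57% instead of 62% at month 3 for the first source, and lowers the bottom of the ranges to about 12% and 24%.

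**3. How strong an artefact this could make**

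A simulation (n = 400,000) gave the month-6 change no predictive value but lowered it by an assumed amount in those who had already stopped. Its correlation with the 12-month sum depends on that amount:

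| Assumed drop after stopping | Correlation |
|---|---|
| 0.25 SD | 0.07 to 0.10 |
| 0.5 SD | 0.14 to 0.20 |
| 1.0 SD | 0.27 to 0.39 |

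The documents give no value for the drop, so this shows that an artefact can arise, not how large it is. Among those still active at month 6 the simulated correlation with later adherence was 0.00, but that is built into the set-up and is not evidence.

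**4. Numbers left at a month-6 landmark, if restricted to those not yet stopped**
- First source: 200 × 0.14 = 28.
- Second source: 200 × (1 − 0.337) = 133 to 200 × (1 − 0.274) = 145.

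**The case against.** The strongest reply is that change scores appear only in an aim sentence. They could belong to the phenotyping rather than the prediction, and the operational text defines no change score. The five IGT learning scores fit a single administration, although two are planned. That ambiguity is real. But the sentence covers prediction and phenotyping together, and nothing limits the model to start-of-study values. Even if values rather than changes are used, month-6 values are not excluded.

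Several stronger readings are tempting, and the documents do not support them:
- **That a late first IGT biases the result.** Three months is an upper limit, the Recruitment section places the IGT with the enrolment assessments, and no mechanism is given by which stopping exercise would alter IGT performance. What remains is that some target weeks may precede it.
- **That a Type D change score contradicts the protocol.** The cited finding is that "this 14-item questionnaire was observed to be stable over 3 months and not dependent on mood and health status", whereas the study interval is 6 months. If the trait is stable, stopping should not move it, which argues against reverse influence for this predictor.
- **That the analysis sample is selected on the outcome.** This presumes a complete-case analysis. The article states no missing-data rule, and that may properly sit in a plan not shown.
- **That the outcome is over when the predictors are measured.** The target is a count of weeks without a quit event, a lapsed participant can resume, and 26 weeks remain. The overlap is partial.

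The study is also a feasibility exercise. That lowers expectations of precision, but prediction remains its stated hypothesis.

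**Conclusion.** The point holds as a fault in what the article states. Month-6 predictors are set against a target of which about 26 of 52 weeks came earlier. The resulting association would be partly concurrent or reverse, most clearly for status of change, which shares the target's criterion. It cannot support identification in advance.

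The overlap in weeks follows directly from the stated schedule. Its effect on the results is unknown. A reader might take the gym dropout figures as this study's rate of stopping. They describe gym membership rather than failure to reach WHO minutes on a tracker, and all but the 86% at month 6 are interpolated. Any simulated correlation rests on an assumed drop after stopping. Not every predictor is late, because start-of-study questionnaires are also collected. That is why the fault can be corrected without new data.

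**What to change.** **Main model.** Use the start-of-study questionnaires and the first IGT only, and send the IGT together with the enrolment questionnaires, as the Recruitment section implies. Define the target as the proportion of adherent weeks among the weeks after the participant's own first IGT. A raw sum would not do: follow-up could run from 39 to 52 weeks, so two fully adherent participants could score 39 and 52.

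**Secondary model.** Use month-6 values and changes only in a landmark analysis predicting the proportion of adherent weeks in weeks 27 to 52. Either include adherence in weeks 1 to 26 as a covariate, or restrict to participants still active under a definition written down beforehand.

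**Cost.** Analysis wording and an earlier notification for the first IGT. The article reports recruitment as pending at submission. If data collection has since started, the analysis changes remain possible without the earlier notification, at the price of more weeks lost. The main model loses the weeks before the first IGT, few if it is sent at enrolment. The landmark model has a shorter target and, if restricted to those still active, possibly far fewer participants: about 28 of 200 under the first cited source. The covariate version avoids that restriction.
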